### Randomisation procedure

2.7

Randomisation will proceed according to a strict simple (non-stratified) protocol, following consenting, using the Qualtrics™ Survey software which uses the Mersenne Twister algorithm to determine allocation to intervention or control group. The RA will not reveal allocation to the participant, nor will anyone else. The only other person who will have access to group allocation data is the Study Manager.

The RA will continue with the Harti tool or inform usual care participants that they will return to go over the final short satisfaction with hospital experiences Mārama survey before they are discharged.

Because the intervention is whānau/family focussed, study contamination will occur if members of the same household are allocated to different intervention groups. Thus, for any child where another sibling or tamariki/child living in the same household has previously been consented and randomised in the trial, the subsequent child will be allocated to the same intervention group as their household member.

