### Design

2.2

The study uses a Kaupapa Māori methodology with qualitative and quantitative methods. Qualitative methods include in-depth interviews with whānau and are published elsewhere (24). Quantitative methodology was a randomised controlled observer-blinded parallel groups single centre superiority trial. It is designed to measure the impact of the Harti tool, compared with usual hospital care, on child and whānau wellbeing outcomes, as specified in the primary and secondary endpoints. Tamariki and their whānau will be randomised to the intervention and control groups at a ratio of 1:1. The intervention group will receive usual care plus the Harti tool, and the control group will receive usual hospital care only, as per the trial schematic shown in Figure 1.

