### Sample size calculation

2.8

We aim to recruit a total of 1,000 participants, of whom we expect approximately 40% will be Māori (based on current figures and expected acceptability of the research protocol). This sample has been calculated to ensure that there is sufficient statistical power to detect a 7% absolute reduction in the 30-day readmission risk in the intervention group for all children and a 12% absolute reduction in the 30-day acute readmission risk for Māori. Sample size calculations are based on a two-tailed 0.05 level of significance with 80% power. We assume that the acceptability of participation will be similar for Māori and non-Māori.

We will measure differences between the intervention and control groups in the primary endpoint (readmission risk) controlling for age, sex, residing in Hamilton, socioeconomic deprivation (NZiDep), and RA responsible for conducting the intervention. Analyses of the primary endpoint will be stratified by ethnicity.

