### Informed consent

2.9

The adult/s accompanying the child and the child will be approached by the RA who will engage using the process of whānaungatanga and values of whakamana and manaakitanga. The RA will introduce herself/himself, and explain the study in broad terms, saying what participation may involve, including matching the child's National Health Index (NHI) number against health outcome databases, plus giving the opportunity to ask questions and give time to consider participation.

Whānau will be provided a brief verbal summary of the study, including the main aims and processes of enrolment. Those that do consent to taking part in the study will be asked to sign consent forms. Those that do not consent will receive usual hospital care. At the time of consent, parent/s/caregivers will be asked if any other children in the household have been consented into the study. If so, the child will be allocated to the same intervention group (as outlined above). Participants will be informed they can withdraw their child, and/or themselves from the trial at any time, but that analysis of collected data will be on-going.

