### Data handling and monitoring

2.23

Analysis will be performed on an intention to treat basis. That is, endpoints will be compared for the two groups as defined from the point of randomisation to intervention or control group. For the primary endpoint, participants who are readmitted multiple times from each group will be included in the analysis only for the first (valid) occasion on which they are readmitted in the 12 months following the index admission.

Bivariate analyses comparing groups will test for statistical significance using the Chi Square test for differences in proportions. For the length of stay secondary endpoint where a difference in medians is to be tested, the Mann–Whitney *U* test will be used.

Although the randomised design is expected to yield balanced intervention and control groups in a study of this size, logistic regression analysis will be used for the primary and secondary endpoints to control for important confounding variables and to facilitate the assessment of interaction variables that increase or decrease the efficacy of the Harti tool. Statistical significance will be tested at the alpha level of 0.05. We will control for the false discovery rate in the secondary endpoints using the Benjamini–Hochberg method (39).

The study is not powered to detect ethnic differences in the impact of the intervention (effect modification). However, we will nevertheless conduct exploratory tests for effect modification with ethnicity (Māori/non-Māori), gender (male/female excluding other), and deprivation (as a dichotomised variable) using the Breslow Day test for homogeneity of odds ratio, and standard maximum likelihood methods (likelihood ratio tests) based on binomial regression models. We will assume an additive interaction for these analyses and report the relative excess risk due to interaction (RERI) where this is significant effect.

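### Later children of a household take the first child's group, so the household is the effective unit of allocation, but the stated child-level tests make no allowance for this

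*Protocol article*

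**What the plan says.** Section 2.2 has tamariki and their whānau "randomised to the intervention and control groups at a ratio of 1:1". Section 2.7 describes simple, non-stratified randomisation after consent. To avoid contamination within a family, it then makes an exception for a child whose household already has a randomised child: "the subsequent child will be allocated to the same intervention group as their household member". Section 2.9 gives the mechanism: "At the time of consent, parent/s/caregivers will be asked if any other children in the household have been consented into the study".

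Section 2.23 fixes the tests: "Bivariate analyses comparing groups will test for statistical significance using the Chi Square test for differences in proportions". It adds a Mann-Whitney U test for length of stay and logistic regression for the primary and secondary endpoints, all by intention to treat from the point of randomisation. Section 2.8 lists the adjustment variables for the primary endpoint as age, sex, Hamilton residence, NZiDep and research assistant (RA). Household is not among them, and the article mentions no clustered variance, mixed model or first-child analysis.

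Shared households are recognised in part. Section 2.19 (Hypothesis 5) uses eligible households as the denominator and counts each once. Hypothesis 4 is framed by household in Table 2 and by parent or caregiver in section 2.18.

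**The concern.** A later child of an enrolled household is not randomised. One random draw assigns the whole household, while the stated tests treat each child as a separate draw. If outcomes of children in one household are positively correlated, those tests understate the standard error. The article gives reasons to expect such correlation: many admissions are respiratory infections (Introduction), housing and household smoking are treated as drivers of illness (2.18, 2.19), and one caregiver may answer the satisfaction survey for two children (2.16).

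A second issue is not cured by a better variance. A later sibling enters after the household has had either the Harti assessment or usual care, and section 2.10 shows the tool acting on other children at home. Whether that sibling is admitted, and whether he or she is behind on services at admission (the denominator of Hypothesis 3, section 2.17), could depend on the group. The group could also be foreseen before the sibling is enrolled. Either would mean that later entrants differ between arms for reasons other than chance.

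**Working it through.** **Inputs from the protocol.** Section 2.8: "We aim to recruit a total of 1,000 participants, of whom we expect approximately 40% will be Māori"; "Sample size calculations are based on a two-tailed 0.05 level of significance with 80% power". The overall target is to "detect a 7% absolute reduction in the 30-day readmission risk in the intervention group for all children". For Māori the target is a drop of 12 percentage points. At 1:1 this is 500 per arm overall and about 200 per arm for Māori.

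**The plan's own figure.** The total of 1,000 cannot be reproduced directly, because no 30-day control risk is stated. Solving the two-proportion formula (pooled variance, no continuity correction) for 80% power gives a control risk of about 22.9% falling to 15.9% overall, and about 30.4% falling to 18.4% for Māori. These implied risks are used below only to express the loss of power.

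**Inputs assumed.** The share *s* of children in two-child households is taken as 5-20%, and the within-household ICC as 0.1-0.3. The protocol states neither.

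**Design effect.** A child alone contributes variance weight 1, and a child in a pair contributes 1 + ICC. Hence DE = (1 − *s*) + *s*(1 + ICC) = 1 + *s* × ICC.

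**Actual type I error of the unadjusted test.** 2 × [1 − Φ(1.96/√DE)].

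**Power with a correct variance.** The two-proportion power at 500/DE per arm, 22.9% against 15.9%. The total that restores 80% power is 1,000 × DE.

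| *s* | ICC | DE | √DE | Type I error | Power | N for 80% |
|---|---|---|---|---|---|---|
| 5% | 0.1 | 1.005 | 1.0025 | 5.06% | 79.8% | 1,005 |
| 5% | 0.3 | 1.015 | 1.0075 | 5.17% | 79.4% | 1,015 |
| 10% | 0.1 | 1.010 | 1.0050 | 5.11% | 79.6% | 1,010 |
| 10% | 0.3 | 1.030 | 1.0149 | 5.35% | 78.8% | 1,030 |
| 20% | 0.1 | 1.020 | 1.0100 | 5.23% | 79.2% | 1,020 |
| 20% | 0.3 | 1.060 | 1.0296 | 5.70% | 77.7% | 1,060 |

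The unadjusted standard error is too small by 1 − 1/√DE: from 1 − 1/1.0025 = 0.25% to 1 − 1/1.0296 = 2.9%.

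**Simulation check.** A beta-binomial simulation of the unadjusted test (1,000 children, 20% risk in both arms, 10,000 runs) rejected in 4.7% of runs at *s* = 5%, ICC 0.1 and in 5.7% at *s* = 20%, ICC 0.3. The Monte Carlo standard error is about √(0.05 × 0.95/10,000) = 0.2 points. The simulation supports the order of magnitude but is too coarse to separate neighbouring rows.

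**Selection.** No arithmetic applies. Sections 2.7 and 2.9 fix a later child's group once the household link is known. Section 2.24 says that the RA knows the allocation and that the whānau may guess it. Sections 2.10 and 2.17 give the routes by which earlier exposure could alter entry and service status. Direction and size cannot be derived.

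**The case against.** The best defence is that the effect is small and the missing detail belongs in an analysis plan that is not shown. A later entrant must be a second child aged 0-4 from the same household, acutely admitted to one hospital between July 2018 and December 2019, approached and consented. Such children may be few. Keeping households together is a sound guard against contamination, and naming logistic regression does not rule out a robust variance. The point about size stands. The point about detail stands only in part: the article itself names plain chi-square and Mann-Whitney tests and lists the adjustment variables, and these do not match its allocation rule.

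A reader might infer three stronger claims, which the document does not support:

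- *That only Hypothesis 5 avoids counting households twice.* Hypothesis 4 is framed by household or caregiver. Its text does not spell out removal of duplicates, but it does not describe counting by child either.
- *That the ICC approaches 1 because one caregiver's referral is counted for two children.* At *s* = 5-20% that would give DE 1.05-1.20 and type I error 5.6-7.4%. The referral endpoints are the two just named, however, and no other endpoint is shown to come near that correlation.
- *That concealment is lost and later siblings are selected and partly treated.* Section 2.9 asks whether another child has been consented, not into which group. The article does not say whether the question precedes signature, whānau are not told their group, and the RA at consent need not be the one who enrolled the first child. These are plausible risks, not documented facts.

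**Conclusion.** The mismatch holds: the household is the effective unit of allocation, and the analysis stated for the primary endpoint and the other child-level endpoints ignores it. On the assumed ranges (5-20% of children in pairs, ICC 0.1-0.3) the nominal 5% test has a true level of about 5.1-5.7%. The error vanishes if within-household correlation is nil, and is smaller still if later siblings are rare. It would not by itself discredit a clear result, but it could matter for a p-value near 0.05. The possible bias from later siblings' predictable group and prior household exposure, chiefly for Hypothesis 3, is inferred from the text and of unknown size and direction. The point merits correction before analysis. It is not a fundamental flaw in the trial.

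**What to change.** Keep the household allocation rule and change the analysis to match:

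1. State that the household is the unit of allocation, and carry a household identifier in the analysis data.
2. For the child-level endpoints, replace the plain chi-square and logistic tests with models that use household-clustered robust standard errors (GEE or sandwich).
3. For the length-of-stay medians (Hypothesis 6), replace the plain Mann-Whitney test with a cluster-aware rank test or a bootstrap that resamples households.
4. Pre-specify a sensitivity analysis of the primary endpoint and Hypothesis 3 restricted to the first randomised child per household. This addresses the selection risk, which clustered variances do not.
5. Report the number of later-entering siblings by arm, so that readers can judge the size of the issue.

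The cost is wording and a little programming, because the household link is already asked for at consent. Confidence intervals become slightly wider (up to about 3% on the assumed ranges), and the sensitivity analysis loses the later siblings.

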### Sample size calculation

2.8

We aim to recruit a total of 1,000 participants, of whom we expect approximately 40% will be Māori (based on current figures and expected acceptability of the research protocol). This sample has been calculated to ensure that there is sufficient statistical power to detect a 7% absolute reduction in the 30-day readmission risk in the intervention group for all children and a 12% absolute reduction in the 30-day acute readmission risk for Māori. Sample size calculations are based on a two-tailed 0.05 level of significance with 80% power. We assume that the acceptability of participation will be similar for Māori and non-Māori.

We will measure differences between the intervention and control groups in the primary endpoint (readmission risk) controlling for age, sex, residing in Hamilton, socioeconomic deprivation (NZiDep), and RA responsible for conducting the intervention. Analyses of the primary endpoint will be stratified by ethnicity.

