As in other parts of Aotearoa, persistent, unfair and unjust inequities in access to material resources and health outcomes exist between communities in the Waikato region of NZ (4, 7). As in other parts of the country, the greatest inequities in resources and outcomes lie between the Indigenous and non-Indigenous populations. This is also true for the paediatric population. More than a quarter of Māori in the Waikato live in the most socioeconomically deprived area (Quintile 5), according to the NZ Deprivation Index (8). In 2013, two in five Māori children lived in households with low equivalised annual household incomes (under $15K) (8). This unequal distribution of wealth is a major driver of inequities in child health outcomes. Even after accounting for unequal distribution of wealth, stark inequities in hospitalisations between tamariki Māori and non-Māori remain. Only ten percent of children aged 0–4 years in Waikato are tamariki Māori, yet tamariki Māori accounted for 44% of hospital admissions for children aged 0–4 years in the winter months of 2014 (9). Of these children, most (71%) were admitted to hospital with a preventable medical condition that had a social gradient, meaning that children from areas of low deprivation had lower disease rates than those from higher deprivation areas (9). These diseases included acute bronchiolitis (43% of the winter admissions in this age group in 2014), pneumonia (11%), asthma (6%) and acute upper respiratory tract infections (4%). Of deep concern is that 51% of tamariki Māori admitted with diseases of poverty were re-hospitalised (at least once) within the next 6 months. At 12 months, for all causes of admission, the risk of readmission for Māori was 56% (9). At the time of the study, in a reported attempt to drive improvements in health spending, health delivery and health equity, a quality improvement target for the NZ Ministry of Health was developed to reduce readmissions for preventable conditions for tamariki aged 0–4 (10).

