### Baseline data collection

2.5

Recruitment and baseline data collection will be the responsibility of a RA who will be present, when possible, on the wards seven days per week. At the start of each day, a RA will generate a list of patients currently on the paediatric ward, screen them for eligibility, and check whether they have already been consented. RAs will check with the ward charge nurse to see if it is appropriate to approach the whānau of eligible patients. A record will be kept of all patients screened for eligibility to be approached and participate in the trial. Reasons for non-eligibility and/or refusal to participate will be recorded in a tracking sheet. Each RA will assure whānau that they have no obligation to provide a reason for non-participation in the trial. At the time of obtaining informed consent a baseline enrolment ascertainment form will be completed. The ascertainment form will record socio-demographic information (age, ethnicity and gender of tamariki patient and caregiver), method of transport to hospital, household size and structure, housing type and number of bedrooms, and level of material deprivation or NZiDep (33). The ascertainment form will be entered online using Qualtrics™ survey software.

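### The combined all-children test of 30-day readmission does not clearly account for ethnicity, which the trial already collects; including it is a small, free gain in precision

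*Protocol article*

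**What the plan says.** Section 2.8 (Sample size calculation) names the adjustment set for the primary endpoint: "controlling for age, sex, residing in Hamilton, socioeconomic deprivation (NZiDep), and RA responsible for conducting the intervention". The sentence after it provides for ethnic stratification of the primary-endpoint analyses. Section 2.13 (Primary endpoint) plans ethnic-specific results and also a result for Māori and non-Māori combined. Section 2.23 (Data handling and monitoring) assigns logistic regression to the control of important confounders and lists ethnicity among the exploratory tests of effect modification.

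Three other places bear on the choice:

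- Section 2.5 (Baseline data collection): the ascertainment form records "socio-demographic information (age, ethnicity and gender of tamariki patient and caregiver".
- Section 2.7 (Randomisation procedure): "Randomisation will proceed according to a strict simple (non-stratified) protocol".
- Section 1 (Introduction): "Even after accounting for unequal distribution of wealth, stark inequities in hospitalisations between tamariki Māori and non-Māori remain".

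**The concern.** Hypothesis 1 concerns all children. Its adjustment set is spelled out and contains deprivation but not ethnicity. By the Introduction's own account, deprivation does not absorb the ethnic gradient in hospitalisation, so NZiDep cannot be assumed to stand in for ethnicity. Nothing in the allocation scheme balances ethnicity between arms. If the combined estimate comes from a model with only the five listed covariates, two things follow. A chance imbalance in Māori share stays in the headline estimate, and any outcome variation that ethnicity explains beyond the listed covariates stays in the error. The trial is built around ethnic inequity, so readers of the result are likely to ask about this first.

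**Working it through.** **Inputs from section 2.8.** "We aim to recruit a total of 1,000 participants, of whom we expect approximately 40% will be Māori", so about 500 per arm, of whom about 200 are Māori. The targets are absolute falls of 7 points overall and 12 points among Māori, with 80% power at a two-sided 5% level. Allocation is 1:1 (section 2.2). The control-group 30-day risk is not given, overall or by ethnicity, so every risk below is an assumption.

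**1. The plan's own figure.** Without a control risk, N = 1,000 cannot be reproduced directly. It can be solved backwards from

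n per arm = [1.96·√(2p̄(1−p̄)) + 0.842·√(p₁(1−p₁) + p₂(1−p₂))]² / (p₁−p₂)²

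- 500 per arm and 7 points give a control risk of about 0.229 (about 0.21 to 0.22 with continuity correction).
- 200 per arm and 12 points give about 0.304 in Māori (about 0.27 to 0.29 with correction).
- The implied non-Māori risk is (0.229 − 0.4 × 0.304)/0.6 ≈ 0.179. The risk ratio is 0.304/0.179 ≈ 1.7 and the gap is 0.304 − 0.179 = 0.125.

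**2. Chance imbalance.** The SD of the difference in Māori share between arms is √(0.4 × 0.6 × 2/500) = 0.031, so the 95% limit is 1.96 × 0.031 ≈ 0.061. The shift in the unadjusted risk difference is this limit times the ethnic gap in risk. At control risk 0.217, which lies in the continuity-corrected range above:

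- risk ratio 1.25 (0.247 v 0.197): about 0.3 points
- risk ratio 1.5 (0.271 v 0.181): about 0.55 points
- risk ratio 2.0 (0.310 v 0.155): about 0.9 points

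The risks implied in step 1 give 0.125 × 0.061 ≈ 0.008, or about 0.8 points. The limit treats children as independent. Section 2.7 puts later children of a household in that household's arm, which could widen it; this is not quantified here.

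**3. Gain from including ethnicity.** R² = 0.4 × 0.6 × (gap)² / [p(1−p)], and effective n = 500/(1−R²). For example, at control risk 0.217 and risk ratio 1.5, R² = 0.24 × 0.0904²/(0.217 × 0.783) ≈ 0.0115 and effective n ≈ 506 per arm. Power for 7 points:

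| Control risk | Without | RR 1.25 | RR 1.5 | RR 2.0 | RR 2.5 |
|---|---|---|---|---|---|
| 0.15 | 0.936 | 0.936 | 0.937 | 0.940 | 0.944 |
| 0.217 | 0.819 | 0.820 | 0.824 | 0.832 | 0.841 |
| 0.30 | 0.709 | 0.711 | 0.716 | 0.732 | 0.749 |

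At the risks implied in step 1, R² = 0.24 × 0.125²/(0.229 × 0.771) ≈ 0.02, and power moves from 0.80 to about 0.81.

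**4. Check on the logistic scale.** The R² formula is a linear approximation, so logistic models with and without ethnicity were simulated at control risk 0.217, with 4,000 runs per setting. Power without/with ethnicity was 0.822/0.822 (risk ratio 1.25), 0.820/0.823 (1.5) and 0.816/0.828 (2.0). With no treatment effect, the rejection rate was 0.044 to 0.052 whether or not ethnicity was in the model.

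These figures describe ethnicity on its own. With NZiDep already in the model the increment would be smaller, in so far as deprivation and ethnicity overlap.

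**The case against.** The strongest reply is that the plan does use ethnicity. A stratified analysis is a recognised way to account for a baseline factor, and a stratifying variable is not normally repeated among the covariates. The homogeneity test named in section 2.23 works across strata, and models for effect modification normally carry a main effect. This is also a condensed article, and the way strata are combined may be set out in an analysis plan that is not shown.

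Part of this stands. A reader might infer that ethnicity is ignored and its information discarded. The planned ethnic-specific analyses contradict that, and the article does not exclude pooling across strata. But no section describes pooling. Section 2.13 sets ethnic-specific results beside a combined one, which reads most naturally as separate estimates plus an overall one. The effect-modification tests are exploratory and do not adjust the Hypothesis 1 estimate. The covariate list is also fixed in the article itself, so its content can fairly be questioned.

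A second reply also stands: the Introduction's statement concerns hospitalisation, not 30-day readmission among children already admitted. Its readmission figures (51% at 6 months, 56% at 12 months) are for Māori, with no non-Māori comparator. A reader might take ethnicity to be an established predictor of the primary endpoint after NZiDep; the document does not show that.

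**Conclusion.** The point holds as a minor improvement to the analysis. The named covariates omit ethnicity, and the combined test of Hypothesis 1 does not clearly account for it. Under assumed control risks of 0.15 to 0.30 and risk ratios of 1.25 to 2.5, including it adds about 0 to 2 power points in most cases. The gain reaches about 4 only at control risk 0.30 with risk ratio 2.5. An imbalance at the 95% limit would move the unadjusted estimate by about 0.3 to 0.9 points at control risk 0.217 and risk ratios 1.25 to 2.0.

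A reader might go further and conclude that the primary estimate is biased or its test invalid. Neither follows. Under randomisation the imbalance is chance variation that the confidence interval already reflects, and the simulated type I error was about 0.05 either way.

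Prior acute admissions might also be suggested as a covariate. That is optional at most. The article gives no figure for their prognostic strength for this endpoint, they are not among the listed baseline items, and a 12-month count is not comparable for infants younger than 12 months.

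**What to change.** In section 2.8, add ethnicity (Māori/non-Māori) to the covariates of the combined all-children model. Alternatively, state that the combined estimate is pooled across the two ethnic strata. Leave the ethnic-specific estimates and the exploratory effect-modification tests as planned. The cost is one line of text, with no new data, since ethnicity is already on the ascertainment form. The model already conditions on five covariates, so a sixth does not change the kind of estimate reported.
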